# The effect of eye movement desensitization and reprocessing (EMDR) on abdominal pain in patients with irritable bowel syndrome (IBS): a study protocol for a randomized controlled trial (EMDR4IBS)

**DOI:** 10.1186/s13063-023-07784-1

**Published:** 2023-12-04

**Keywords:** Irritable bowel syndrome, IBS, Eye movement desensitization and reprocessing, EMDR, Treatment, Abdominal pain, Quality of life, QoL, RCT, Study protocol, Linear mixed effects model

## Abstract

**Background:**

Irritable bowel syndrome (IBS) is a highly prevalent disorder for which treatment options such as medication, diets, and hypnotherapy either have shown limited effect or relieve symptoms in only a limited subset of patients. Abdominal pain is the key criterion for the diagnosis and is deemed the most distressing IBS symptom, and the most disruptive of everyday life. A growing body of research demonstrates the effect of Eye Movement Desensitization and Reprocessing (EMDR) on chronic pain. EMDR is known as a safe and successful treatment for disorders in which unresolved traumatic memories play a role in the cause or maintenance of symptoms. In IBS, activated memories may increase pain through pain flashbacks and the stress generated by unresolved memories. The aim of this study is to ascertain whether applying EMDR to traumatic memories including pain memories will reduce abdominal pain in IBS patients.

**Methods:**

This study is a randomized controlled trial which will be conducted at a city hospital in the Netherlands. Adult patients with considerable IBS pain (pain intensity at least 60/100 during at least 5/10 days) will be randomly assigned to either EMDR therapy or the wait list. We aim to include 34 participants. The EMDR condition comprises seven sessions, around 90 min in length delivered weekly, the first of which is a case conceptualization session. All participants will be assessed at baseline, post-treatment, and at 3 months follow-up. The primary outcome measure is pain intensity on a Likert scale which is self-reported daily during a 2-week period. Secondary outcomes include similar daily ratings on other IBS symptoms and reported hindrance of valued activities, and also standardized questionnaires on IBS symptoms and Quality of Life. Data will be analyzed by a Linear Mixed Effects Model for repeated measures.

**Discussion:**

The results are expected to gain insight into the effectiveness of EMDR treatment on abdominal pain in IBS. As there are very few effective treatment options for IBS-related abdominal pain, this study could have important implications for clinical practice.

**Trial registration:**

Human ethics committee MEC-U NL71740.100.20. International Clinical Trial Registry Platform: NL8894. Prospectively registered on 28 January 2020.

**Supplementary Information:**

The online version contains supplementary material available at 10.1186/s13063-023-07784-1.

## Administrative information

Note: the numbers in curly brackets in this protocol refer to SPIRIT checklist item numbers. The order of the items has been modified to group similar items (see http://www.equator-network.org/reporting-guidelines/spirit-2013-statement-defining-standard-protocol-items-for-clinical-trials/).

## Introduction

### Background and rationale {6a}

Irritable bowel syndrome (IBS) is a common chronic disorder of brain-gut interaction. Its etiology is most likely multi-factorial involving biological, psychological, and social factors. The self-reported prevalence of IBS in the Netherlands is 15–20% in women and 5–20% in men [1]. Not only do symptoms of IBS have great impact on the individual’s quality of life [2], but it also causes a significant burden to the health care system and society at large [3]. The Rome criteria are developed and updated by an international group of experts and are used to diagnose IBS in clinical care and clinical trials. The Rome IV criteria [4] for IBS feature altered bowel habits and stool changes, but the key criterion, and a requirement for the diagnosis, is “frequent abdominal pain”.

IBS pain is often described as sharp, stabbing, cramping, or throbbing. Pain intensity may be continuous or change throughout the day, the unpredictability making it difficult to plan activities (either social or work-related).

Abdominal pain has been found to be the most distressing IBS symptom, as well as the most disruptive, having a great impact on the quality of life [5, 6]. Up to 16% of IBS patients in secondary care have contemplated suicide, because of symptom severity, i.e., pain intensity, interference with life, and lack of effective treatment [7]. Conventional pain medication is not suitable for treating IBS pain [8]. The effectiveness of drugs such as NSAIDs or opiates in alleviating IBS pain is low, and they have considerable side effects, sometimes even aggravating pain in the long run. Although other treatment options such as diets, laxatives, and antispasmodics can relieve pain in some patients, in general, patients are dissatisfied with their overall efficacy and tolerability [9]. This has led the Dutch IBS guideline for General Practitioners to center its recommendations on educating the patient, reducing anxiety and avoidance behaviors, and promoting healthy life style choices. In cases of a severely reduced quality of life, the guideline suggests either antidepressants or psychological treatment [10]. Often, patients prefer the last option. Of these psychological treatments for IBS, so far, hypnotherapy appears to be most effective in pain reduction [11–16]. However, a review shows that response rates found in different studies vary widely [14]. Hence, the search for effective treatments of abdominal pain in IBS continues.

In the last decades, there has been a growing body of research on the effect of eye movement desensitization and reprocessing (EMDR) on chronic pain. EMDR is known as a successful and widely embraced treatment for post-traumatic stress disorder (PTSD) and other disorders in which unresolved traumatic memories play a role in the cause or maintenance of symptoms [17–19]. Four systematic reviews, published in 2009, 2014, 2016, and 2019 [20–23], conclude that EMDR is an effective treatment for chronic pain. Clinical practice and several published case studies established that traumatic experiences involving physical pain can cause pain flashbacks. These pain flashbacks are usually very similar to the original pain in terms of location and quality [24–27] and can be triggered by both internal and external trauma-related cues. Activated pain memories can maintain current pain through pain flashbacks and the stress generated by unresolved memories [28].

Research into the pathogenesis of abdominal pain in IBS appears to confirm this notion. In IBS, neurobiological research has shown altered processing of signals along the gut-brain axis. These changes appear to be related to pain-related expectations and learning processes [29]. It is suggested that when interoceptive memories of aversive visceral states develop, they may allow the brain to recall visceral experiences of pain in the form of constant or recurrent pain [30].

A successful EMDR treatment in PTSD helps patients (re)process traumatic memories, thereby reducing memory vividness, emotionality, and hypervigilance. In (re)processing the traumatic pain memories, we expect to reduce their chronic (re)activation, optimizing the circumstances for recovery and thereby reducing pain intensity. We designed this study to ascertain whether applying EMDR to traumatic memories including pain-related memories will reduce abdominal pain in IBS patients. Although clinical practice shows promising results, to our knowledge, no research into the effect of EMDR on abdominal pain in IBS has been conducted.

## Objectives {7}

The primary objective of this study is to assess the effect of EMDR treatment on abdominal pain in IBS. It is hypothesized that participants in the EMDR treatment condition will show a greater reduction in abdominal pain intensity than those in the wait-list control group.

Our secondary objectives are to determine the effects of EMDR treatment on (1) other salient IBS symptoms (personalized), (2) overall severity of IBS-related symptoms, (3) the hindrance of valued activities caused by abdominal pain (personalized), (4) quality of life, and (5) the reported rate of adequate relief from IBS symptoms.

It is hypothesized that EMDR treatment will, as compared to the wait-list control condition, lead to a significantly greater reduction of salient symptoms, the overall severity of IBS symptoms, and the experienced hindrance of valued activities. Furthermore, we hypothesize that quality of life will show greater improvement in the treatment condition (EMDR) than in the wait-list control condition, and that after treatment and at follow-up, a higher percentage of patients in the treatment condition (EMDR) will indicate experiencing “adequate relief” of IBS symptoms than in the wait-list control condition.

## Trial design {8}

The present study is a superiority study comparing the EMDR intervention with a wait-list control group in a two-armed randomized controlled trial. Patients will be randomly allocated to either EMDR treatment or wait list, with an equal allocation ratio. Blinding for the intervention is not possible.

This study is registered at The Netherlands Trial Register, with registration number NL8894. It is thereby automatically included in the International Clinical Trial Registry Platform.

For an overview of the study design, including recruitment, random allocation, assessments, and treatment, see Fig. 1.

**Fig. 1 Fig1:**
[figure not shown]
Inclusion flowchart

## Methods: participants, interventions, and outcomes

### Study setting {9}

Participants will be recruited from the general hospital Diakonessenhuis, Utrecht area in the Netherlands.

### Eligibility criteria {10}

Detailed inclusion and exclusion criteria are listed in Table 1.

**Table 1 Tab1:** Detailed inclusion and exclusion criteria

Inclusion criteria	
1	Age 18–65
2	Meet Rome IV diagnostic criteria for IBS
3	A pain intensity score of at least 60 (on a scale of 0–100)
4	Frequency of abdominal pain at least 5 out of 10 days
5	Informed consent
Exclusion criteria	
1	Insufficient proficiency in the Dutch language, or any other circumstances interfering with communication or completing questionnaires
2	Psychiatric problems such as psychosis, severe depression, or suicidality requiring immediate treatment
3	Ongoing trauma-focused treatment, such as EMDR, trauma-focused Cognitive Behavioral Therapy (tCBT), and Imaginary Exposure (IE)
4	Any other medical conditions such as Colitis or Crohn’s disease in which abdominal pain is a key symptom
5	Pain in another area of the body which is more prominent than abdominal pain
6	Ongoing drug abuse (excluding nicotine or caffeine abuse) interfering with EMDR therapy
7	Self-reported pregnancy or planned pregnancy within the next 5 months. Sensations in the abdomen caused by the pregnancy might be difficult to distinguish from the sensations caused by IBS

Subjects are eligible for participation if they meet Rome IV criteria for IBS and report severe pain intensity at least half of the time. Severity of pain is measured by the self-reported pain intensity score on the Irritable Bowel Syndrome—Severity Scoring System (IBS-SSS). A pain intensity score of 60 or more on a scale of 0–100 is considered to reflect “severe pain.”

The Rome IV criteria [4] are:

Recurrent abdominal pain, on average, at least 1 day/week in the last 3 months, associated with two or more of the following:Related to defecationAssociated with a change in frequency of stoolAssociated with a change in form (appearance) of stool.

Criteria need to be fulfilled for the last 3 months with symptom onset at least 6 months prior to diagnosis.

Participants are allowed to continue any prior IBS treatment such as medication or a diet as long as they agree not to change these during the trial.

Treatment will be administered by qualified psychologists who have been included in the Dutch legal register for Professions in Individual Health Care (BIG-register) and are at least EMDR Europe accredited level 1 trained in EMDR therapy.

### Who will take informed consent? {26a}

The gastroenterologist establishes whether subjects meet Rome IV criteria for IBS. Afterwards, they complete a short questionnaire comprised of the IBS-SSS (short form) to which this question is added: May we invite you to participate in a scientific study of a new treatment for IBS?

Subjects meeting the initial criteria (pain intensity and frequency) receive, by post, the Patient Information Form packet (PIF) approved by the Medical Ethical Committee. About a week later the principal investigator calls the subject to answer questions that may have arisen and to screen for exclusion criteria. If the subject meets inclusion criteria, does not meet exclusion criteria, and is willing to participate, he or she fills out and signs the consent form included in the PIF and sends it to the principal investigator in the included return envelope.

### Additional consent provisions for collection and use of participant data and biological specimens {26b}

Standard items in the consent form state that the participant agrees thathe or she has been informed satisfactorily about the study and that enough time was given to form a well-founded opinion on participation.he or she has chosen to participate voluntarily, and he or she is free to stop participation without having to give a reason.she knows she cannot participate when pregnant.

and agrees tothe principal investigator informing both their gastroenterologist and general practitioner of their participation in the study and of any unexpected findings concerning their health.the collection of data in order to answer the study’s research questions.allow the study process controllers specified in PIF, access to their data.the therapy sessions being videotaped to check for treatment adherence and fidelity.

Additionally, the participant is asked to state whether they consent tobeing recognizable in de session video tapes.their personal information and data being used in future studies on either EMDR or IBS.being approached, after this study, to participate in follow-up research.

### Interventions

#### Explanation for the choice of comparators {6b}

So far, no scientific research has been done to study the effect of EMDR on pain in IBS. We choose to compare the intervention group with a wait-list control group. Comparison to an active control group such as gut-directed hypnotherapy or psychoeducation would require a larger sample size than we have the means to carry out. The same restrictions in time and resources prevent us from arranging an inactive control condition.

#### Intervention description {11a}

EMDR treatment is based on the eight phases of the EMDR standard protocol [31–33]. Listed below are the principal steps in each phase.History taking: taking history, making a case conceptualization based on the information gathered, and compiling a list of traumatic experiences.Client preparation: explanation of the theory behind EMDR, the introduction of the eye-movement task and tactile and auditory tasks (buzzers, clicks), answering questions, in general preparing the client for EMDR.Assessment: the memory that will be processed in the session is decided on. The target image (the most distressing image of the memory) is identified, as well as the principal negative belief, feelings, and sensations linked to the memory. Also, a positive cognition is chosen. Baseline measures are established for the credibility of this positive cognition (Validity of Cognition, VoC), and the amount of stress generated by the target (Subjective Units of Distress, SUD).Desensitization: taxing working memory while focusing on the target, by applying eye movements, until the SUD score is zero.Installation: strengthening of the positive belief until it feels true.Body scan: the therapist asks the client to bring the original target to mind and check for any residual tension in their body. If so, these physical sensations are then targeted for reprocessing.Closure: consolidation of the positive effects (whether the reprocessing is complete or not), instructions for between sessions and how to reach the therapist when needed.Reevaluation of treatment effect: takes place at the beginning of each new session, to check whether the SUD of previous targets is still low.

After that another memory from the trauma list is chosen, for which the procedure is repeated from phase 3.

A special kind of target is the flash forward, which does not involve a memory, but an image representing a dreaded event in the future. Interweaves can be used when the reprocessing process is blocked or loops. Extra tasks taxing working memory can be used in case of high-stress levels of abreaction.

In this study, the intervention consists of seven weekly 90-min sessions, which include:An intake in which onset, severity, frequency, and impact of IBS symptoms are explored and an overview is made of all the traumatic events related to the onset and/or maintenance of the abdominal pain or negative experiences with the pain. Both PTSD A criterion events such as rape or car accident and adverse events that are not life-threatening such as bouts of severe abdominal pain or instances of (near) defecation in public are included in the overview. Based on the acquired information, a case conceptualization is made, from which the memories to be processed are selected. This concludes phases 1 and 2 of the EMDR standard protocol.Six sessions of EMDR lasting 90 min each in which phases 3 to 8 of the EMDR standard protocol [31–33] are applied to the selected memories. In addition to the customary sets of rapid eye movements, tactile and auditory input (buzzers and beeps) may be applied to optimally tax working memory. During the EMDR sessions, the therapist will direct extra focus/attention to physical sensations, usually abdominal sensations. If relevant, a flash forward will be desensitized. Interweaves will be applied if necessary. Successful desensitization is defined as the reaching of SUD = 0 (Subjective Units of Distress; the recollection of the event no longer causes the subject any distress). If severe abdominal pain remains after having processed all relevant targets, the pain itself will become the focus of the next EMDR session. Treatment is ended either after six 90-min sessions, or when all relevant memories have been successfully desensitized.

Treatment takes place face-to-face. However, if necessary due to quarantine during the COVID-19 pandemic, it can also be offered online via video consultation. Although as yet little is known about the effectiveness of online EMDR treatment for PTSD, so far results are promising that effects may be similar to real-life EMDR treatment [34].

#### Criteria for discontinuing or modifying allocated interventions {11b}

With acquiring new information during sessions, the case conceptualization can change a little, which in turn can change the selection of memories to be processed. The EMDR treatment in itself will not be altered.

Patients are free to withdraw from partaking in the study at any time. The research team can decide to remove a patient from the study if.There are serious medical reasons.The subject fails to complete the questionnaire(s) during the first period of measurements.The subject fails to appear at a treatment session more than twice (without notice).The subject’s non-cooperation seriously hinders treatment.Subject meets an exclusion criterion along the way (e.g., becomes pregnant or an intestinal disease is diagnosed).There are persistent serious side effects.

Like all studies involving human subjects, we are required to report serious adverse events as defined by the Central Committee on Research Involving Human Subjects (in Dutch: CCMO, Centrale Commissie Mensgebonden Onderzoek).

No serious adverse effects have been found in studies of EMDR in diverse populations. Some discomfort—both physical and psychological—both during sessions and in the first 4 days after an EMDR session is not unusual. As this is part of the psychological process of processing negative memories, this is no cause for discontinuing the intervention.

Any unexpected adverse effects will be discussed within the research team, which includes two EMDR Europe registered EMDR consultants with extended expertise. Depending on the outcome of this deliberation, steps will be taken to reduce the adverse effects. If necessary, participation in the study will be temporarily interrupted. If the adverse effects persist, participation in the study will be discontinued.

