## Statistical methods

### Statistical methods for primary and secondary outcomes {20a}

The statistical analyses will be performed according to the intention-to-treat principle.

The primary outcome measure in this study is the reported intensity of abdominal pain, which is registered during 14-day periods of daily diary questions, at three points in time, yielding 42 data points per participant.

The principal research question will be answered by performing a linear mixed effect models analysis, based on 2 groups (treatment and control) and 3 (baseline, after treatment, follow-up) × 14 (days) measuring moments. Before the analysis, data will be checked for outliers and the assumption of linear relations. Values with an absolute *z*-score > 4 will be treated as outliers and removed.

The model will be built in a stepwise model, first fitting an intercept-only linear mixed effects model, allowing to disentangle variance between patients and variance within patients over time. In a second step, the predictor time will be added, to control for any unexplained changes over time in subsequent models. If necessary, a quadratic term for time will be added to the model as well. Subsequently, in the third model, the fixed effect for condition will be added. In the fourth model, the fixed effect for measurement period (baseline, treatment, and follow-up) will be added (note, this variable will represent the difference between baseline and treatment period and baseline and follow-up period irrespective of condition). In the sixth model, the difference between measurement periods will be allowed to vary over patients (a so-called random slope for measurement period). If this is significant, in a seventh model, an interaction between measurement period and condition will be included, to explain why the differences between periods vary over patients. This last term, the interaction between measurement period and condition, answers our primary research question: what is the overall difference in changes in pain score over measurement periods between condition and control group?

After performing the analysis, the assumption of normally distributed errors for both level 1 and level 2 errors will be assessed.

As to the secondary outcome measures: the data gathered from the residual diary questions (pertaining to other IBS symptoms and hindrances experienced in valued activities) are analyzed in the same way as the primary outcome (abdominal pain intensity).

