### Methods in analysis to handle protocol non-adherence and any statistical methods to handle missing data {20c}

Every effort is made to avoid missing data. The way the diary questions and questionnaires are administered online makes it impossible to skip a question. Also, patients who do not complete a questionnaire or diary will receive one or more reminders.

For all analyses, a linear mixed effects model (LMEm) analysis is used. The advantage of linear mixed effects modeling is that the analysis can be performed on all data available, and missing data is handled automatically assuming Missing at Random (MAR) without requiring imputations.

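### Section {11b} lets an unblinded team remove randomised patients from the study on some grounds that only the EMDR arm can meet, in conflict with the intention-to-treat analysis in {20a}

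*Protocol article*

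**What the plan says.** Section {11b} of the protocol article is headed as criteria for stopping or changing the allocated intervention, but its rule concerns the study: "The research team can decide to remove a patient from the study if" one of several conditions is met. The conditions include:

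- "The subject fails to appear at a treatment session more than twice (without notice";
- that the subject's "non-cooperation seriously hinders treatment";
- "The subject fails to complete the questionnaire(s) during the first period of measurements";
- serious medical reasons, an exclusion criterion met during the trial (pregnancy and intestinal disease are the examples), and persistent serious side effects.

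The same section adds, on unexpected adverse effects: "If the adverse effects persist, participation in the study will be discontinued".

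On analysis, {20a} states: "The statistical analyses will be performed according to the intention-to-treat principle". Section {20c} relies on a mixed model because "the analysis can be performed on all data available, and missing data is handled automatically assuming Missing at Random (MAR) without requiring imputations".

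Other sections set the context. The envelope is opened after consent ({16b}), and the main investigator tells the participant the result ({16c}). Participants and therapists cannot be blinded ({17a}). Diaries are kept only at inclusion, 8 weeks and 20 weeks ({12}). The primary question is answered by the interaction of measurement period and condition ({20a}), tested one-sided at 0.05.

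**The concern.** Intention-to-treat needs outcome data on everyone randomised, whatever happens to their treatment. Section {11b} treats ending therapy and leaving the trial as one event and leaves the decision to a team that knows the allocation.

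Only EMDR patients have sessions to miss, therapy to hinder, or side effects of EMDR. Removals on these grounds therefore have no counterpart on the wait list. If the patients removed are those who are doing badly, the EMDR mean improves while the wait-list mean stays as it is. The primary contrast then shifts towards EMDR for a reason unrelated to its effect. With at most 34 participants, one or two such removals matter.

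**Working it through.** **1. Which grounds can arise in which arm**

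| Ground in {11b} | EMDR | Wait list |
|---|---|---|
| Repeated missed sessions | yes | no |
| Non-cooperation that hinders treatment | yes | no |
| Side effects of EMDR | yes | no |
| Incomplete first-period questionnaires | yes | yes |
| Serious medical reasons | yes | yes |
| New exclusion criterion | yes | yes |

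Incomplete first-period questionnaires also come before treatment, because the intake session is the day after the questionnaires ({13}). That ground cannot reflect response to EMDR.

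**2. What a removed patient leaves behind**

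No diary falls between inclusion and week 8. A patient removed during the weekly sessions, and not measured afterwards, has at most 14 of the 42 planned diary scores, all at baseline. Such a patient adds almost nothing to the period-by-condition interaction. Under missing at random, the model in effect assumes that the patient would have followed the same course as the EMDR patients who stayed, given baseline pain. Attendance, cooperation and in-session distress are not in the model described in {20a}. If they relate to both removal and later pain, the assumption fails.

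**3. Size if removed patients have no benefit**

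The article gives no figure for removals, so there is none to reproduce. Inputs: 34 participants ({14}) allocated 1:1 ({16a}), taken as 17 per arm. Assumptions: m EMDR patients are removed, each has zero benefit, and the rest are analysed as completers with mean benefit b.

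- Mean benefit over all 17 = b × (17 − m)/17
- Estimate from those who remain = b
- Ratio of estimate to truth = 17/(17 − m)

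Results:

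- m = 1: 17/16 = 1.063, an overstatement of 6%
- m = 2: 17/15 = 1.133, 13%
- m = 3: 17/14 = 1.214, 21%

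This ratio multiplies a true effect. If the true effect is zero, the bias is zero, so it says nothing about false positives.

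**4. False-positive risk under selective removal**

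A simulation with no true effect used 17 per arm, normal change scores with SD 1, and k EMDR patients removed by a score whose correlation with poor response is rho. The test was a two-sample t-test at one-sided 0.05, with 40,000 runs. The values of k and rho are assumptions, and one change score stands in for the mixed model. With nobody removed, type I error was 0.050.

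| Removed (k) | rho = 0 | rho = 0.3 | rho = 0.5 | rho = 1 (the worst k) |
|---|---|---|---|---|
| 1 | 0.050 | 0.063 | 0.070 | 0.103 |
| 2 | 0.049 | 0.071 | 0.091 | 0.163 |
| 3 | 0.050 | 0.084 | 0.110 | 0.224 |

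The corresponding bias for k = 2 is about 0, 0.07, 0.11 and 0.21 SD.

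**The case against.** The case on the other side has real weight.

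- **The article never says that removed patients give no further diaries, or that their data are deleted.** Section {20c} would keep whatever they have supplied, and {17a} shows that a missed session can simply move the questionnaire dates. A reader might infer that the analysis cannot be intention-to-treat. The text does not go that far. What stands is that removal from the study, in its ordinary meaning, ends data collection, and nothing in the article says otherwise.
- **Removal is discretionary, and no post-baseline diary would normally exist when it is decided.** The team could not select on diary scores. Therapists may have clinical impressions and consultants see weekly session checklists ({11c}), so selection is possible, but it is not shown.
- **Nothing shows that patients who miss sessions respond poorly.** A reader might infer that the rule strips poor responders from the EMDR arm. That is plausible, but it is not documented.
- **Several grounds reach both arms.** The one-sided concern cannot be extended to the whole list.
- **The step from 24 to 34 participants in {14} might be read as an expected loss of 10/34 = 29% through such removals.** The article states no drop-out rate and calls 34 a maximum. The allowance covers loss of any kind in both arms.
- **This is a condensed article.** The full protocol may settle how removed patients are followed, and that detail is not a finding here. The conflict between {11b} and {20a} remains because both rules are stated in the article.

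**Conclusion.** The point holds as a conflict between stated rules that can bias the primary contrast. Section {11b} allows removal from the study after randomisation, partly on grounds that only EMDR patients can meet and by a team that knows the allocation. Section {20a} promises intention-to-treat. Section {20c} relies on an assumption that fails if removal is linked to unrecorded poor response.

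The bias could favour EMDR, but neither its direction nor its size is established. The 6%, 13% and 21% for one, two or three removals assume no benefit in those removed, a completer analysis and 17 per arm. For two removals, one-sided type I error would be about 0.07 to 0.09 under moderate selection (rho 0.3 to 0.5) and 0.16 if the two worst responders left. If removal is unrelated to response, it stays near 0.05. The higher values in the table need exactly the worst responders to be removed and should not be taken as the expected case.

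**What to change.** Reconcile {11b}, {20a} and {20c} by formal amendment:

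- State that the listed grounds may end study treatment. The clinical grounds themselves stay unchanged.
- Keep sending randomised participants the 8- and 20-week online diaries and questionnaires unless they withdraw consent for data collection.
- Analyse all data in the allocated arm.
- Report removals by arm and reason.
- Reconcile this with the pregnancy wording in the eligibility table ({10}) and the consent items ({26b}). As written, these bar participation during pregnancy, so they bear on whether measurement may continue.

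The online tool and reminder calls already exist ({12}, {18b}), so the running cost is a few more e-mails and calls. The change affects study conduct, so under {25} it needs approval from the ethics committee and the institutional review board before use. Some patients will decline further measurement. Recruitment was due to end on 31 December 2023, so the change helps only patients whose diaries are still due. Diaries never collected from patients already removed cannot be recovered.
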